#### Safety measures

Safety measures are displayed in Table 4.

**Table 4 Tab4:** Safety measures

Outcome	Measure	Pre	Post (4.5 months)	Post (10.5 months)	Source of collection
*Safety measures*	Admissions	x		x	register
	Deaths	x		x	register
	Suicide	x		x	register

### Assessment tools

#### Personal recovery

*Questionnaire for the process of recovery (QPR):* Personal recovery is measured using the Questionnaire for the process of recovery (QPR), a validated 15-item measure of personal recovery as conceptualised within the CHIME framework and developed in Britain as a collaboration between clinicians and mental health service users [53, 54, 74, 99, 114]. Each item is answered using a 5-point Likert scale with anchors “strongly disagree” and “strongly agree”, resulting in a range of 0–60. A mean difference of 4 has been considered relevant [53].

*Thwarted belongingness scale (TBS):* The recovery dimension of connectedness is measured using Thwarted belongingness scale (TBS), a validated 8-item measure of the subjective feeling of isolation and connectedness [39, 60]. Each item is answered on a 7-point Likert scale with anchors “not at all true for me” and “true for me”, resulting in a range of 8–56. A mean difference of 14 has been considered relevant [60].

#### Self-efficacy

*Self-efficacy for personal recovery scale (SEPRS):* Self-efficacy is measured with the Self-efficacy for personal recovery scale (SEPRS) [112], which comprises 14 items on the form “How confident are you that you can…”. Each item is answered on a scale from 1–100, resulting in a range of 14–1400.

#### Functioning

*The Work and Social Adjustment Scale (WSAS):* Impairment in social functioning is measured by the validated Work and Social Adjustment Scale (WSAS) [69]. WSAS is a self-report 5-item scale that assesses functioning on a scale from zero to eight. The sum score ranges between 0 and 40. A mean difference of 9 has been considered relevant [69]⁠.

#### Quality of life

*The Manchester Short Assessment of Quality of life (MANSA):* Quality of life is measured using the Manchester Short Assessment of Quality of life (MANSA). MANSA is a validated 16-item self-report questionnaire, developed primarily for persons with schizophrenia spectrum disorders and comprising items on whether the person i) has a friend ii) has a friend that s/he has seen in the last week, iii) has been accused of a crime, and iv) has been the victim of violence, as well as 12 items on satisfaction with occupation, activities, relationships, health, and living and financial situation [12, 84, 88]. The 12 items are answered on a 7-point Likert scale with anchors “couldn’t be worse” and “couldn’t be better”, resulting in a sum score in the range 12–84. A mean difference of 4 points has been considered relevant [11].

#### Mentalising

*Mentalization scale (MentS):* Mentalising is measured with the Mentalization scale, which is a validated 28-item scale consisting of three subscales Self-Related Mentalisation, Other-Related Mentalisation, and Motivation to Mentalise [3, 29]. It is scored on a 5-point Likert scale, resulting in a score range of 28–140. A mean difference of 8 has been considered relevant [29].

*Toronto Alexithymia Scale (TAS):* Alexithymia is measured using Toronto Alexithymia Scale (TAS), a validated 20-item scale with three subscales: difficulty describing feelings, difficulty identifying feelings, and externally oriented thinking, i.e., low motivation and habit to reflect on feelings [6, 7, 47, 66, 108]. Each item is answered on a 5-point Likert scale with anchors “not at all true for me” and “to a high degree true for me”, resulting in a range of 20–100. A mean difference of 7 has been considered relevant [66].

#### Additional assessment tools for the pilot RCT

*The Screen for cognitive impairment in psychiatry (SCIP):* The Screen for cognitive impairment in psychiatry (SCIP-D, Danish version) is used to measure cognitive performance [89]. The SCIP-D is a validated screening tool for detecting cognitive impairment in persons with psychotic and affective disorders [10, 80, 93]. A low score signifies more impairment. A mean difference of 3.6 has been considered relevant [97].

*Positive and Negative Syndrome Scale (PANSS-6):* The severity of positive and negative symptoms is measured by the Positive and Negative Syndrome Scale (PANSS-6), which is a 6-item clinician-rated scale measuring delusions, conceptual disorganisation, hallucination, blunted affect, social withdrawal, and lack of spontaneity in conversation. Each item is rated from 1–7, giving a possible score between 6 and 42 [48, 78, 79].

*Global Assessment of Functioning Scale – function (GAF-F):* Social function is measured using the Global Assessment of Functioning Scale – function [82, 86]. GAF-F is an interview-based, clinician-rated estimate of social function including occupational function, for which 4 points on a 100-point scale has been proposed a minimum clinically relevant effect ⁠[1, 23].

*The Awareness of Social Inference Test (TASIT):* Social cueing is measured with The Awareness of Social Inference Test (TASIT) [13]⁠, subsection 2A [44, 63]⁠. The TASIT assesses social cueing using videos of naturalistic everyday conversations in which two actors interact. Participants are asked questions about the communicative intentions of the people in the clips. The total accuracy score takes values in the range of 0–60. A mean difference in accuracy of 4 has been considered relevant [13]⁠.

*Visual perspective-taking task (VISPT):* Balancing of the other-perspective is measured with the Visual perspective-taking task (VISPT) [95]⁠. A computer-based task measuring ability or tendency to ignore another person’s perspective in one’s visual perception, and ability or tendency to take another person’s perspective into account in one’s visual perception judgments. Participants view an avatar in a room, with a number of discs on the walls: in one condition (consistent) the avatar sees the same number as the participant, in the other (inconsistent) the number differs. Correct scores range from 0–36 with correctness on consistent compared to inconsistent trial computed as a ratio [52, 100]⁠.

### Assignment of interventions

After baseline data are obtained, the participants are randomly allocated to either the control (standard mental healthcare) or active group (REWRITALIZE + standard mental healthcare) with a 1:1 allocation using the randomisation module in REDCap (Research Electronic Data Capture) [41, 42]. The randomisation sequence will be generated by an external researcher at Copenhagen Research Centre for Mental Health (CORE) and uploaded to REDCap. The randomisation is stratified by sites. Varying block sizes, unknown to the research team, are used. To ensure concealment, the randomisation schedule is stored away from the research team and the block sizes are not disclosed. Participants randomised to the control group will be set on a waiting list and will be informed that they will be offered to participate in a creative writing group within one year of the randomisation.

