**Methods:**

The RCT is an investigator-initiated, randomised, two-arm, assessor-blinded, multi-center, waiting-list superiority trial involving 300 participants (age > 18) from six psychiatric centers in regions Capital and Zealand in Denmark, randomised to receive either the creative writing intervention combined with standard treatment or standard treatment alone. Assessments will be conducted before and after the intervention and at six months post intervention. The primary outcome is personal recovery at the end of intervention measured with the questionnaire of the process of recovery. Secondary outcomes include other measures of personal recovery, self-efficacy, mentalising, and quality of life. The pilot RCT, integrated within the RCT, will focus on 70 of the participants aged 18–35 with schizophrenia spectrum disorders, evaluating exploratory measures related to perspective-taking, social cognition, cognitive function, psychosocial functioning, and symptom pressure.

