### Participants

Participants in the RCT will be included in the study if they are over 18 and diagnosed with a severe mental illness, i.e., schizophrenia, schizotypal, delusional, and other non-mood psychotic disorders, bipolar disorder, severe depression, posttraumatic stress disorder, or borderline personality disorder (F2, F31, F32.2, F32.3, F33.2, F33.3, F43.1, F60.3). Forensic psychiatric patients will be excluded. In all, 30–34 groups, 15–17 active groups and 15–17 control groups, will be carried out with 8–10 participants in each group. Although power calculations (see below: Sample size and power calculations) set the minimum sample size to 266 and the RCT intention-to-treat principle reduces the threat of drop-out for power, we will aim to include 300 participants. Considering the relatively high drop-out rate in similar interventions [64, 110], the enhanced inclusion enables us to aim for a higher number of real, as opposed to imputed, follow-up data, and to minimise the risk to end up with low power if participants were to retract their informed consent.

Participants in the pilot RCT will be included in the study if they are between 18 and 35 and fulfil the criteria for a schizophrenia spectrum disorder (F20, F21) according to the Present State Examination [87, 115].

Participants will be recruited from outpatient clinics’ OPUS programs (early intervention program for first episode psychosis) and F-ACT (Flexible Assertive Community Treatment) at Mental Health Centres in Regions Capital and Zealand in Denmark [40, 75, 109].

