#### Sample size and power calculations

The minimum sample size is calculated based on the ability to detect a minimal but clinically significant difference between the active intervention group and the control group in the primary personal recovery QPR measure. The minimal clinically significant difference between the study groups has been estimated to 4 points [53]. Based on trials in similar populations, we assume a standard deviation of 10 in the study population, which corresponds to an effect size of Cohen’s* d* = 0.4 [104, 114]. To achieve a statistical power of 90% at a significance level of 5%, a total of 266 participants must be included in this study to detect a difference: 133 in each group. Based on the needed participants, power calculations for secondary outcomes were calculated and are presented in Table 6. Because of the relatively high drop-out rate in the pilot study and similar studies [64, 110], we will plan for a sample size of 150 participants in the active group and 150 participants in the control group. This should hence allow for at least a 90% power of finding a minimally clinically significant difference in the primary measure, i.e., the QPR measure of personal recovery.

**Table 6 Tab6:** Power

**Outcome**		**Measure**	**Alpha**	**Mean diff**	**SD**	**Cohen’s *****d***	**Power**	***n***	**Mean diff source**	**SD source**
*Primary*			0,05							
	Personal recovery	QPR		4	10	0,40	0,9	266	[53]	[114]
*Secondary*										
	Connectedness	TBS	0,05	14	14	1	1	266	[60]	[60]
	Self-efficacy	SEPRS	0,05	x^a^	x	0,40	0,9	266		
	Functioning	WSAS	0,05	5	7	0,71	1	266	[69]	[69]
	Quality of life	MANSA	0,05	4	11	0,36	0,83	266	[11]	[11]
	Overall mentalising	MentS	0,05	8	12	0,66	1	266	[29]	[29]
	Alexithymia	TAS	0,05	7	11	0,63	1	266	[66]	[47]

See Table 5 and the assessment tool section for outcome measure abbreviations

^a^Power estimates for measures for which no relevant mean difference was identified are based on a moderate to small effect size of Cohen’s* d*=0.4

For the pilot RCT no calculation of sample size has been made as the primary aim for a pilot RCT is to explore design uncertainties before proceeding to a future RCT [35], here feasibility of chosen measures.

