#### Data analyses

The main outcome measure is personal recovery measured by QPR. To test the research hypothesis, the differences at follow-up between the active intervention group and the control group will be analysed using independent-samples t-test⁠. Effect sizes to judge clinical relevance will be estimated by Cohen’s d [19]. All variables are continuous. Secondary and exploratory measures will be tested by the same means. The significance level is set to 0.05 for all measures. If there, despite randomisation, are differences in any baseline measure between active and control groups, these differences will be adjusted for in the comparison between active and control groups using general linear models.

Data analyses will be based on the intention-to-treat principle. Data from all participants will thus be included in the analyses. In accordance with the principle, missing data from the follow-up will be imputed using multiple imputations by means of Markov Chain Monte Carlo methods in Stata. All co-variates of supposed prognostic significance will be used to impute a distribution of missing data. A prerequisite for multiple imputation is that data are missing at random. This will be examined by various means, e.g. by comparing prognostic baseline characteristics between the participants for whom follow-up data are missing and the participants for whom follow-up data have been collected.

As a supplementary analysis, the differences at follow-up between the active and control groups will be analysed including only observed data, i.e. data for whom follow-up data have been collected. A detailed statistical analysis plan will be prepared and uploaded to clinicaltrials.gov before initiating analyses.

For the pilot study mean, standard deviation, within and between group differences on the outcome measures will be calculated.

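### Randomisation is stratified by site, but the planned t-test leaves site out; if site is prognostic for the QPR, a little precision is lost that one sentence would recover

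*Protocol article*

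**What the plan says.** The abstract places the 300 participants in centres described as "from six psychiatric centers in regions Capital and Zealand in Denmark". Under Assignment of interventions, allocation is 1:1 in blocks of varying size, and "The randomisation is stratified by sites".

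Under Data analyses, the primary comparison is fixed: "the differences at follow-up between the active intervention group and the control group will be analysed using independent-samples t-test". Secondary and exploratory measures are to be tested in the same way. General linear models come in only under a condition that begins "If there, despite randomisation, are differences in any baseline measure between active and control groups". Site is not among the participant characteristics in Table 1. No section puts site in a between-arm comparison. The imputation text uses every covariate thought to be prognostic, without naming site. A detailed statistical analysis plan is promised before analysis; it is not at hand.

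**The concern.** Stratified blocks keep the arms close to balanced on site. A site effect common to both arms therefore largely cancels from the arm difference. The t-test does not use this: its pooled standard deviation still contains the between-site variation, so its standard error describes an unstratified allocation.

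The conditional rule does not repair the mismatch. It responds to differences between the arms, and site is the factor on which the design prevents them. The rule may admit covariates that differ by chance while leaving out the one factor the trial controls.

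If site predicts QPR, the interval is wider than the design warrants as far as site is concerned, the test is somewhat conservative, and part of what stratification bought is not collected.

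**Working it through.** **Inputs from the article (Sample size and power calculations).** The target difference: "The minimal clinically significant difference between the study groups has been estimated to 4 points". The standard deviation: "we assume a standard deviation of 10 in the study population". Significance level 5% (taken as two-sided, which the article does not state), power 90%, 133 per arm.

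**The plan's own figure.** Normal approximation: n per arm = 2 × (1.96 + 1.2816)² × (10/4)² = 131.3, so 132. The exact t-test calculation gives 132.3, so 133 per arm and 266 in total. The stated sample size is reproduced. Power at 133 per arm is 90.4% (normal) or 90.1% (exact t).

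**Assumption.** The article gives no between-site variance. Let r be the share of QPR variance due to a site effect common to both arms, with the total standard deviation held at 10 and site treated as exactly balanced. I use r = 0%, 2%, 5% and 10%.

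**Formulas.**
- t-test standard error: 10 × √(2/133) = 1.226; 95% half-width 1.96 × 1.226 = 2.40 points.
- True standard error under stratification: 1.226 × √(1 − r).
- Excess width of the t-test interval: 1/√(1 − r) − 1.
- True type I error of the t-test: 2 × [1 − Φ(1.96/√(1 − r))].
- Power of the t-test: Φ((4 − 2.40)/(1.226 × √(1 − r))).
- Power with site in the model: Φ(4/(1.226 × √(1 − r)) − 1.96).

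| Site share r | True SE | Half-width with site | t-test interval too wide by | True type I error of t-test | Power, t-test | Power, site in model |
|---|---|---|---|---|---|---|
| 0% | 1.226 | 2.40 | 0% | 5.0% | 90.4% | 90.4% |
| 2% | 1.214 | 2.38 | 1.0% | 4.8% | 90.6% | 90.9% |
| 5% | 1.195 | 2.34 | 2.6% | 4.4% | 90.9% | 91.7% |
| 10% | 1.163 | 2.28 | 5.4% | 3.9% | 91.5% | 93.0% |

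These figures are before any loss from drop-out or clustering.

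**Check by simulation.** With 300 participants, six sites, 25 per arm per site, no treatment effect, r = 10% and 4,000 runs, the mean t-test standard error was 1.143 against a true value of 1.084, with type I error 3.9%. With site as a fixed factor the mean standard error was 1.094 and type I error 4.7%. This agrees with the formulas.

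**Clustering, for contrast.** The Participants section plans 15–17 active groups of 8–10. I added a group effect in the active arm only (three groups per site, 18 in all, and an assumed intraclass correlation of 0.05) to a 5% site share. Type I error was then 6.5% for the t-test and 7.3% with the site term. The net error can thus lie above 5%, and adding site alone does not bring it back.

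**The case against.** The strongest reply is that nothing here threatens a conclusion. The t-test remains valid as far as site is concerned and errs on the safe side. On the figures above it keeps power over the 90% target, and the site term adds only 0.3, 0.8 or 1.5 percentage points at shares of 2%, 5% and 10%. If site explains nothing, there is no loss. This stands, and it sets the size of the point.

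It can also be said that model terms are often settled in the statistical analysis plan, and that the imputation sentence would already take in site if site is prognostic. Both are partly right. But the article does more than stay silent: it names a test without site and a condition for adjustment that site would not meet. Naming site in the imputation text is a clarification.

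A reader might go further in four ways that the article does not support:
- **That the interval is too wide as a matter of fact.** No between-site variation in QPR is reported. The Participants section names OPUS and F-ACT as sources but does not say that their mix varies by site.
- **That the planned test is safely conservative overall.** It also ignores clustering in the writing groups, which works in the opposite direction.
- **That differences between conductor-tandems are part of this site effect.** Tandems act only in the active arm before the last assessment, so their differences are not common to both arms and do not cancel.
- **That the Discussion claims a consistent effect across sites.** It says only that the multicentre design may ease implementation.

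**Conclusion.** The mismatch between randomisation and analysis is real: site is a stratification factor, the named test omits it, and the adjustment rule would not bring it in. The consequence is conditional and modest. If site accounts for 2–10% of QPR variance, the interval is 1.0–5.4% too wide as far as site is concerned; at 0% it is correct. Type I error is not inflated by this omission. The size rests on the assumed site share, a common site effect in both arms, near-exact balance within sites, and the article's standard deviation of 10. Clustering needs its own remedy. This is a free improvement, not a flaw that endangers the primary result.

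**What to change.** In Data analyses, state that every between-arm comparison in the full sample uses a linear model with site (the randomisation stratum) as a fixed factor, whether or not the arms differ at baseline. Name site in the imputation model as well. A display of the QPR difference by site, descriptive and without a test, is optional.

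The cost is one or two sentences and five degrees of freedom (six sites; with 266 participants the residual degrees of freedom fall from 264 to 259). No new data are needed. Fixing the term in advance also removes one choice from the analyst.

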### Blinding

Owing to the nature of the intervention, neither participants, nor staff can be blinded to allocation. Participants will be instructed not to disclose the allocation status to the researchers. Baseline data will be collected prior to randomisation and those who collect follow-up data will be blinded. An employee outside the research team will extract data from REDCap on study completion, and group allocation will be coded with A and B to ensure blinding of the researchers during analysis and interpretation of data, drawing conclusions, and writing reports.

### Data collection and analysis

#### Data collection

Data will be collected at baseline and at follow-ups at 4.5 and at 10.5 months after baseline (see Table 5). After informed consent forms have been signed, participants can choose to fill out the questionnaires while the research assistant stays with them on Teams, or they can choose to do it after the meeting. Data collection for these active groups and their controls will commence approximately a month prior to group start and stop at the second follow-up at 10.5 months after group start. For each participant that drops out, the reason for drop-out will be registered. All participants who have not withdrawn their consent will be contacted for follow-ups, including those who decided to stop the intervention before it ended. For the pilot RCT data will be collected at baseline and follow-up at 4.5 months after baseline.

**Table 5 Tab5:** Schedule of enrolment, interventions, and assessments

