### Objectives

Objective 1 of this study is to determine if REWRITALIZE as supplement to standard mental healthcare is more effective than standard mental healthcare alone for promoting personal recovery, as measured by the Questionnaire for the process of recovery (QPR) immediately after the end of the intervention, in a sample of individuals with severe mental illness.Objective 2 is to investigate if REWRITALIZE as supplement to standard mental healthcare is more effective than standard mental healthcare alone in promoting mentalising, self-efficacy, functioning and quality of life, as measured at the end of the intervention, and in promoting personal recovery six months after the end of the intervention.Objective 3 is to explore REWRITALIZE as supplement to standard mental healthcare for advancing clinical recovery variables, specifically cognition and social cognition, and pilot-test if REWRITALIZE leads to symptom reduction and improve psychosocial function in a smaller sample of participants with schizophrenia spectrum disorders.

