### RCT design

The RCT is designed as an investigator-initiated, randomised, two-arm, assessor-blinded, multi-center, waiting list-controlled superiority trial. The allocation ratio to active and control condition is 1:1. The participants (*n* = 300) will be randomised to active condition (REWRITALIZE plus standard treatment) or waiting list control condition (standard treatment) (see Randomisation below). As it is a waiting list control group, the persons randomised to the control group will be invited to participate in a creative writing group after the last assessment (within one year). To ensure high methodological quality, the trial is designed and will be reported according to the SPIRIT 2013 Statement and the modified CONSORT 2017 criteria for non-pharmacological trials [15, 17]. Data will be collected at baseline, at the end of the intervention (approximately 4.5 months after baseline) and six months after the end of the intervention (approximately 10.5 months after baseline). A flow chart of the study is provided in Fig. 2.

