### Intervention

REWRITALIZE is conceptualised as a hybrid between an art group and a group therapy intervention [16]. It is developed by an interdisciplinary group of professional authors, user experts, and researchers, and it is manualised ([name], [name], [name]: Manual for REWRITALIZE, forthcoming).

REWRITALIZE consists of 15 three-hour sessions, 14 weekly with an additional session after a one-month break to reduce the risk of adverse effects at the end of the intervention. During the sessions, the 8–10 participants are presented with literary forms that function as prompts for writing exercises. Participants write spontaneously on the presented form for 5–15 min. After each text is read out loud, the participants engage in a reflective discussion about the text. The primary conductor, a professional writer with teaching experience, secures high artistic standards. S/he is supplemented by a co-conductor with clinical expertise who participates in the group activities together with the other participants and ensures psychological safety. Together they constitute the conductor-tandem. The exercises are presented during the course of sessions to participants in an order securing adherence to group therapeutic principles.

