#### Outcome measures

In Table 2 the primary and secondary outcome measures are listed. The primary outcome measure is the Questionnaire about the process of recovery (QPR) which measures personal recovery as understood within the CHIME framework [74, 99, 114] measured at the end of the intervention, i.e. approximately 4.5 months after baseline. Secondary outcome measures include QPR six months after the end of the intervention (10.5 months after baseline), as well as other measures of personal recovery, mentalising, self-efficacy, functioning and quality of life measured at 4.5 months.

**Table 2 Tab2:** Primary and secondary measures

**Outcome**		**Measure**	**Pre**	**Post (4.5 months)**	**Post (10.5 months)**	**Source of collection**
*Primary*						
	Overall personal recovery	QPR	x	x		SR
*Secondary*						
	*Personal recovery*					
	Overall personal recovery	QPR	x		x	SR
	Connectedness	TBS	x	x		SR
	Self-efficacy	SEPRS	x	x		SR
	Functioning	WSAS	x	x		SR
	Quality of life	MANSA	x	x		SR
	*Mentalising*					
	Overall mentalising	MentS	x	x		SR
	Alexithymia	TAS	x	x		SR

*SR* self-report questionnaire*; QPR* Questionnaire for the process of recovery; *TBS* Thwarted belongingness scale; *WSAS* Work and Social Adjustment Scale; *SEPRS* Self-efficacy for personal recovery scale; *MANSA* Manchester Short Assessment of Quality of life; *MentS* Mentalization scale; *TAS* Toronto Alexithymia Scale

The explorative outcome measures are shown in Table 3. These include the secondary measures at the 10.5 months follow-up in the full sample. The outcome measures for the active group at 4.5 months and 10.5 months, respectively, will be compared to the outcome measures for the control group at 4.5 months and 10.5 months, respectively (see Data analysis).

**Table 3 Tab3:** Exploratory measures

Outcome	Measure	Sample	Pre	Post (4.5 months)	Post (10.5 months)	Source of collection
*Exploratory*						
Connectedness	TBS	full	x		x	SR
Self-efficacy	SEPRS	full	x		x	SR
Functioning	WSAS	full	x		x	SR
Quality of life	MANSA	full	x		x	SR
Overall mentalising	MentS	full	x		x	SR
Alexithymia	TAS	full	x		x	SR
Cognition	SCIP-D	subsample	x	x		T
Social cueing	TASIT 2A	subsample	x	x		T
Balancing of other-perspective	VISPT	subsample	x	x		T
Positive and negative symptoms	PANSS-6	subsample	x	x		CR
Functioning	GAF-F	subsample	x	x		CR

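### Follow-up is counted from baseline in most places but from group start in one, so for participants enrolled early the 4.5-month primary assessment may fall before the last session

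*Protocol article*

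**What the plan says.** The primary time point is defined by an event. Objectives gives it "as measured by the Questionnaire for the process of recovery (QPR) immediately after the end of the intervention".

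Two sections then attach an approximate calendar time to that event. RCT design has the first follow-up "at the end of the intervention (approximately 4.5 months after baseline" and the second "six months after the end of the intervention (approximately 10.5 months after baseline". Outcome measures has the primary QPR "measured at the end of the intervention, i.e. approximately 4.5 months after baseline".

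Data collection uses the calendar alone, without naming the event or marking the times as approximate: "Data will be collected at baseline and at follow-ups at 4.5 and at 10.5 months after baseline". It repeats 4.5 months after baseline for the pilot RCT. A later sentence in the same paragraph, about the active groups and their controls, says that collection "will commence approximately a month prior to group start and stop at the second follow-up at 10.5 months after group start".

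The Intervention section sets the length of the programme: "15 three-hour sessions, 14 weekly with an additional session after a one-month break". Assignment of interventions and Blinding place baseline before randomisation, and so before group start. Table 5 labels its time points t-1 to t4 without calendar values, so it does not settle the origin.

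**The concern.** Baseline and group start are different dates, and the article itself puts up to about a month between them. The same 10.5 months cannot run from both. The article also treats the end of the intervention and 4.5 months after baseline as one time point, which holds only for certain lead times between baseline and the first session.

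At stake is when QPR is measured for Objective 1, and whether the second follow-up, a secondary outcome, really comes six months after the programme ends. The lead time can differ between participants, so a baseline origin also lets the number of days from last session to assessment differ between them. Controls have no end-of-intervention event of their own, so their visit dates depend on whichever calendar origin is used.

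**Working it through.** **Inputs**
- Sessions: 14 weekly, then one more after a one-month break (Intervention).
- Lead from baseline to group start: collection opens about one month before group start (Data collection). Individual leads are not stated, so I vary the lead from 0 to 1 month.
- Visits: 4.5 and 10.5 months (RCT design, Outcome measures, Data collection).
- Assumptions: 1 month = 30.44 days. The exact date of session 15 is not given, so I place it three ways.

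**Length of the programme from group start**

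Session 14 is 13 weeks after session 1: 13 × 7 = 91 days, or 2.99 months.
- A: session 15 four weeks later: 91 + 28 = 119 days = 3.91 months.
- B: one month later: 91 + 30.4 = 121.4 days = 3.99 months.
- C: 14 full weeks, then one month: 98 + 30.4 = 128.4 days = 4.22 months.

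**Reproducing the stated 4.5 months**

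End of intervention from baseline = lead + programme length. Setting this to 4.5 gives a lead of 4.5 − 3.91 = 0.59 (A), 4.5 − 3.99 = 0.51 (B) or 4.5 − 4.22 = 0.28 (C) month. The stated figure is therefore right for a baseline about 0.3 to 0.6 month before group start. It does not reproduce at a one-month lead, where the end of intervention is 4.91, 4.99 or 5.22 months after baseline.

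**4.5 months after baseline against session 15**

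Days after session 15 = (4.5 − lead) × 30.44 − programme days. A negative value means before session 15.

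| Lead (months) | A | B | C |
|---|---|---|---|
| 0 | +18.0 | +15.5 | +8.5 |
| 0.5 | +2.8 | +0.3 | −6.7 |
| 1 | −12.5 | −14.9 | −21.9 |

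At a one-month lead the visit falls (4.5 − 1) × 30.44 = 106.5 days after group start. That is after session 14 and inside the break.

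**Second follow-up**
- From baseline, one-month lead: 10.5 − 1 − 3.91 = 5.59 (A), 5.51 (B) or 5.28 (C) months after session 15.
- From group start: 10.5 − 3.91 = 6.59 (A), 6.51 (B) or 6.28 (C) months after session 15.
- Gap between the two origins: equal to the lead, so at a one-month lead the last visit is at 10.5 or 11.5 months after baseline.

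**Both visits from group start**

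The 4.5-month visit falls 18.0 (A), 15.5 (B) or 8.5 (C) days after session 15, and the second visit is 10.5 − 4.5 = 6 months after the first.

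**Waiting-list promise**

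Controls are to be offered a group within one year of randomisation (Assignment of interventions), after their last assessment (RCT design). If randomisation follows baseline closely (an assumption), a last visit at 11.5 months after baseline leaves 12 − 11.5 = 0.5 month.

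**The case against.** The best defence is that the primary time point is an event and the calendar figure is only a gloss. Objectives names the end of the intervention, and RCT design and Outcome measures mark 4.5 months as approximate. A team that follows the event would measure QPR after session 15. This stands, and it rules out the reading that the primary outcome will not be measured at the end of the intervention.

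Second, one month is when collection opens, so it is roughly the earliest baseline and not every participant's lead. This also stands: with a lead of half a month, the visit is within about a week of session 15 on either side.

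Third, the group-start origin is written only for the second follow-up. A reader might infer that the primary assessment could also come a month later than stated, but no sentence times it from group start.

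Fourth, even in the worst case 14 of 15 sessions are complete. Baseline precedes randomisation, so there is no reason for the lead to depend on the arm. A reader might still infer a bias between arms, with active participants measured at the event and controls by the calendar. At a one-month lead that would separate them by 4.91 − 4.5 = 0.4 to 5.22 − 4.5 = 0.7 month. The article does not say that this will happen, and it mentions the active groups and their controls together.

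The defence does not remove the conflict. Data collection, the section on when visits are made, gives calendar times only and uses two origins in one paragraph. Visit windows can be left to a fuller document, but two stated origins for the same visit are a contradiction in the text itself.

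**Conclusion.** The inconsistency is real and needs correcting, but its size is modest. The second follow-up has two origins up to about one month apart. For participants with baseline a full month before group start, the 4.5-month visit falls about 12 to 22 days before session 15, and the 10.5-month visit comes about 5.3 to 5.6 months after it, short of the stated six. For leads below about 0.3 to 0.6 month the 4.5-month visit is at or after session 15. So for early-enrolled participants the primary assessment may precede its defining event. The documents do not show that it will do so generally, that it will be a month late, or that the arms will be measured at different times.

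These ranges rest on the assumed placement of session 15 and on leads between 0 and 1 month. The waiting-list promise is not contradicted by a last visit at about 11.5 months after baseline, but the margin is thin.

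**What to change.** Reconcile RCT design, Outcome measures and Data collection on one time origin: the start date of the index writing group, shared by the active group and its controls. Both follow-ups are then 4.5 and 10.5 months after that date in both arms, so the first follows session 15 and the second comes six months after the first. Make the same correction to the pilot RCT sentence.

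Then check the corrected last visit against the commitment to offer controls a group within a year of randomisation. For the earliest-enrolled controls, the group-start origin leaves only about two weeks.

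The cost is protocol wording and the scheduling dates in REDCap. No visits are added.
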